# A randomised clinical trial study assessing the efficacy of 5% losartan potassium loaded in ethosomal gel to treat human keloids: a trial protocol

**DOI:** 10.1186/s13063-023-07880-2

**Published:** 2024-01-02

**Keywords:** Angiotensin II, Angiotensin II receptor blocker, Losartan potassium, Triamcinolone acetonide, Efficacy, Randomised clinical trial

## Abstract

**Background:**

Keloid is a skin disorder that results from excessive fibrous tissue growth in the area of the initial trauma. Treating keloids can be challenging since the success of various treatments varies from one study to another. Triamcinolone acetonide injection, a standard treatment, can cause undesirable side effects. Meanwhile, the effectiveness of existing topical therapies for keloids is not always reliable. The pro-inflammatory, pro-proliferative, and pro-fibrotic effects of angiotensin II in human skin contribute to keloid formation. Losartan potassium, an angiotensin II blocker, has the potential to act as an anti-keloid agent. Due to the thicker skin structure of a keloid and ease of application, ethosome gel is chosen as a safe and comfortable carrier for losartan potassium, making it a good choice for treating keloids.

**Methods:**

In this randomised clinical trial, 46 adults with keloids were divided into two treatment groups. One group of 23 participants received 5% losartan potassium loaded in ethosomal gel, while the other group of 23 participants received intralesional injections of 10% triamcinolone acetonide. Over 12 weeks, changes in POSAS 3.0 scores, degree of erythema and pigmentation, surface area, thickness, and pliability of the keloids will be measured at four different times: baseline, 4 weeks, 8 weeks, and 12 weeks. Statistical analysis will be conducted using SPSS software version 24, with a significance level of *p* < 0.05.

**Discussion:**

Losartan potassium is believed to be beneficial for keloid management because it inhibits the angiotensin II receptor, which plays a role in inflammation, proliferation, and fibrosis. This study examines the efficacy of 5% losartan potassium loaded in ethosomal gel for human keloids.

**Trial registration:**

Clinicaltrial.gov identifier NCT05893108. Registered on 7 June 2023.

## Administrative information

Note: the numbers in curly brackets in this protocol refer to SPIRIT checklist item numbers. The order of the items has been modified to group similar items (see http://www.equator-network.org/reporting-guidelines/spirit-2013-statement-defining-standard-protocol-items-for-clinical-trials/).

## Introduction

### Background and rationale {6a}

Keloids and hypertrophic scars result from abnormal skin responses to trauma extending beyond the injury site and may appear years later [1]. Excessive scar tissue can cause pain, itching, and contractures that affect patients’ well-being [2, 3]. Keloid scarring is common among those who have had surgery or suffered trauma. Fifteen per cent of scar tissue can grow excessively, making treatment challenging. However, its prevalence and frequency data could be more extensive and scattered [4].

The cause of hypertrophic scars and keloids is not fully understood, but it is thought that one of the stages of wound healing is interrupted [5, 6]. Cytokines like interleukin (IL), e.g. IL-6, IL-8, and IL-10, may impact scar tissue formation. Furthermore, transforming growth factor-β (TGF-β) is not regulated well; collagen production can increase, leading to scarring. Imbalanced extracellular matrix deposition and degradation may also cause scars during remodelling [5, 7].

The renin-angiotensin system (RAS) is found in all layers of human skin [8], including cells like keratinocytes, fibroblasts, and vascular endothelial with angiotensin type I receptors (AT1R) and angiotensin type 2 receptors (AT2R). Only melanocytes have only AT1R receptors melanocytes [9–11]. Research showed that keloid fibroblasts have a higher expression of AT1R receptors than normal and hypertrophic scar skin [12]. Angiotensin is the ultimate player in the RAS process [13]. The liver produces angiotensinogen, which becomes angiotensin I with the help of renin. Angiotensin-converting enzyme (ACE) and chymase convert angiotensin I to angiotensin II, which has pro-inflammatory, pro-proliferation, and pro-fibrosis effects [14].

Treating keloid and hypertrophic scars is challenging, with no universally effective therapy available [15]. Intralesional triamcinolone acetonide (TAC) corticosteroid injections are the recommended therapy by the International Advisory Panel on Scar Management [16] and are widely used in the USA [17] and Indonesia. It is often used alone or with other modalities [17, 18] but may cause side effects like pain and skin changes [19]. Keloids often recur, even after excision [20]. Some people may be uncomfortable with needles [21]. Topical therapy for keloids and hypertrophic scars has limited options. Studies show varying results for topical drugs [22], but they are pain-free and easy to apply [23]. RAS-targeting topical medications show promise as a new treatment method [24]. In vitro and in vivo studies show that using AT1R inhibitors effectively and safely prevents and treats keloids and hypertrophic scars [25–28]. Human clinical trials have also shown positive results compared to placebo [25, 29–31].

Keloids and hypertrophic scars have a different skin structure than normal skin, with a thicker epidermis and dermis layer [32, 33]. Thus, topical medications are less effective [34, 35]. Scar tissue also has fewer hair follicles, adnexal glands, papillary dermis, and rete ridges than normal skin [36]. These conditions can hinder the penetration of drugs through the skin and lower water retention [37, 38]. Studies have shown inadequate hydration can further reduce drug absorption [34, 35].

To ensure a topical drug works, it must penetrate the skin and reach the target [39]. Thus, nano-sized carriers can help enhance delivery [40]. Lipid-based nanovesicles can effectively treat keloids with their specific skin structure [39], such as ethosome. These nanovesicles are known for their softness and elasticity [41]. Ethosome is superior to other vesicular systems. It can hold more drugs, penetrate deeper into the skin, and trap molecules of varying lipophilicity and is non-toxic for both in vivo and in vitro studies [42–46]. Ethosome is effective in occlusive and non-occlusive conditions and works well for dermal, transdermal, and intracellular delivery. They are also more stable and have smaller vesicle sizes [47]. Losartan potassium as an AT1R inhibitor loaded in ethosomal gel had demonstrated excellent entrapment ability, skin permeation ability, and formulation stability, enhancing the effectiveness of drug application. Animal safety assessments indicated it was irritant-free [48]. This study aims to assess the efficacy of 5% losartan loaded in ethosomal gel (5% LEG) compared to standard treatment based on clinical outcomes changes.

### Objectives {7}

The main goal is to compare the efficacy between 5% losartan loaded in ethosomal gel (5% LEG) and 10 mg/ml triamcinolone acetonide (10 mg/ml TCA) injection for keloid treatment, based on these parameters, i.e. The Patient and Observer Scar Assessment Scale 3.0 (POSAS 3.0) scores, erythema and pigmentation degree using dermoscopy (Heine® iC1) images, keloid surface area using digital photography planimetry (Sony® α6000), keloid thickness using high-frequency ultrasounds (Hitachi® Arietta s60 Japan), and pliability using durometer instrument type oo (Tecklock®Japan).

### Trial design {8}

Our study will follow a randomised controlled trial (RCT) design with a single-blind approach. We will use parallel group superiority trial and unpaired group methods and conclude the investigation by assessing parameter changes within 12 weeks. A block randomisation method is utilised to allocate participants, generating blocks of two with a 1:1 ratio. Randomisation does not distinguish the occurrence of keloids based on skin colour as the research setting tends to have a homogenous population with skin tones typical of Southeast Asians, ranging from light to dark brown [49].

## Methods: participants, interventions, and outcomes

### Study setting {9}

The study focused on patients aged 18 years and above, diagnosed with keloids, who visit the outpatient clinic of the dermatology department at The General Hospital of Syafira Pekanbaru, Riau, Indonesia, between August 2023 and April 2024.

### Eligibility criteria {10}

To qualify for our study, participants must be 18 years old or above and have keloid scars that measure 25 cm^2^ or less. Each participant must have at least one keloid that has lasted for at least 6 months, and they cannot take keloid medication for the past 2 months. Those who are unable to understand the patient and observer scar assessment scale (POSAS), refuse to participate, have nodular keloids, take antihypertensive medication, are pregnant, have a history of allergies, have active skin lesions in the keloid area, or have bleeding or scars are not eligible for the study. Additionally, we will exclude individuals who have undergone keloid treatment within the last month.

### Who will take informed consent? {26a}

The principal investigator will brief participants willing to participate in the study. The study will be explained through an explanatory sheet, and written informed consent will be obtained from participants before enrolling them.

### Additional consent provisions for collection and use of participant data and biological specimens {26b}

Not applicable. No involvement of any biological specimens.

## Interventions

### Explanation for the choice of comparators {6b}

The treatment comparator chosen is the active control intralesional injection of 10 mg/ml triamcinolone acetonide (10 mg/ml TAC). This is because it is the preferred method for treating keloids in some countries, such as Indonesia. However, intralesional steroid injections have several side effects, including pain and skin changes [19]; some people may be uncomfortable with needles [21].

### Intervention description {11a}

Forty-six eligible adolescents with keloid will be randomly assigned to the 5% losartan potassium loaded in ethosomal gel (5% LEG) group (*n* = 23) and active control of triamcinolone acetonide 10 mg/ml (TAC 10mg/ml) groups (*n* = 23). Ethosomal gel bearing 5% losartan potassium will be applied twice daily on the keloid with the rule of fingertips unit (FTU) [50], and 10 mg/ml TAC will be injected intralesionally in the keloid every 2 weeks for 12 weeks with the rule of 0.1 mg/cm^2^ [51]. With a Good Manufacturing Practise (GMP) certificate, the Dion Farma Abadi company will provide 5% LEG. The study patients will receive the intervention gel monthly during the study visit. Ten milligrams per millilitre triamcinolone acetonide (Flamicort®) used in the study is manufactured by Dexa Medica. Our trial has four study visits, i.e. before the intervention or baseline, after 4, 8, and 12 weeks.

### Criteria for discontinuing or modifying allocated interventions {11b}

If any signs of side effects, such as allergies or worsening complaints, are observed during intervention treatment, it will be discontinued immediately. Similarly, in the control injection treatment, the dose will be reduced or stopped if any allergic side effects or skin atrophy are detected or the participant expresses unwillingness to continue the study.

### Strategies to improve adherence to interventions {11c}

We will inform study patients how to use their gel treatment and the schedule of injections, and phone calls will follow them weekly. The compliance evaluation will depend on the quantity of gel left in the tubes and the adherence to injection visit schedules.

### Relevant concomitant care permitted or prohibited during the trial {11d}

While undergoing keloid treatment, patients can continue taking any previously prescribed drugs or supplements. However, it is advised to avoid adding any treatments related to keloid treatment, such as pain or itching relievers drugs, that may interfere with the efficacy assessment of the primary treatment.

### Provisions for post-trial care {30}

Any side effects during the study will be treated as they would in a clinical setting. The serious adverse event form will document any risks beyond minimal or physical injury. If a serious adverse event is found to be causally linked to the research intervention, it will be addressed according to applicable procedures. If the participants derive significant benefits from the new drug intervention, they can continue receiving the treatment as long as the gels are available. Similarly, suppose subjects benefit from the intralesional injection, the active control, and wish to continue with the therapy. In that case, it will be extended for approximately two months after the study concludes.

### Outcomes {12}

The research inquiry will encompass an assessment of both primary and secondary outcomes. The primary outcome directed towards the evaluation of POSAS 3.0 scores. Throughout the study’s duration, we will systematically assess POSAS 3.0 scores at four specific time intervals: the initial baseline assessment upon participants’ first arrival, followed by subsequent evaluations at weeks 4, 8, and 12. This measurement directly correlates with the patient’s quality of life [52]. We will utilise the most up-to-date version of the POSAS 3.0 questionnaire, accessed at https://www.posas.nl. We have received approval from the POSAS team to use this questionnaire and have been granted a license via email. This questionnaire will be translated into Indonesian and tested for validity and reliability before being used in the study. Patients will complete the POSAS 3.0 questionnaire, which includes 16 items. Five of these items are about the current state of their scar tissue, and 11 questions are about how their feeling related to the scar tissue over the past week. Meanwhile, an observer will complete a different section of the questionnaire with seven items scored on a scale of 1 to 5. We will add the PSAS and OSAS scores to determine the total score. The minimum patient score is 16, while the highest score is 80. The minimum and maximum scores for observers are 7 and 35, respectively.

In the context of this study, secondary outcomes encompass the evaluation of erythema and pigmentation levels, as well as assessments of keloid area, thickness, and pliability. These secondary outcome measures at four different time points will be assessed concurrently with the primary outcome.

The colour images will be captured using dermoscopy equipment from Heine® iC1 Germany, followed by image analysis. Dermoscopy is employed to capture colour images from three discrete regions, specifically focusing on the edges and central region. This process is iterated for precision, and subsequently, ImageJ image analysis computes the average colour quantification of the captured images. The same proficiently trained assistant will capture colour images using dermoscopy consistently during the entire duration of the study. Our team will utilise digital photography (Sony®α6000 Japan) and ImageJ image analysis software to examine the surface area. A trained assistant will take pictures of the keloid with appropriate camera lighting, and a ruler will be included in the shot to confirm the scale in ImageJ. The surface area changes will be measured in centimetres squared and evaluated at four different time points throughout the study.

A dedicated computer IT assistant, consistent throughout the study, will measure colour degrees and surface areas using ImageJ to maintain consistency.

High-frequency ultrasound (Hitachi® Arietta s60 Japan) will be employed to assess keloid thickness. The linear probe will be operating at frequency of 5–12 MHz [50]. Throughout the study, the same radiologist will consistently measure the thickness of the keloid in centimetres, specifically assessing it at the same three points as during the initial measurement. Subsequently, the obtained measurements will be averaged for analysis. The pliability of keloids is measured using a manual tonometer called durometer type oo (Tecklock® Japan). A trained assistant will use the tonometer on three different areas of the keloid and calculate the average in durometer units displayed on the device. During the study, we will also monitor for any potential side effects arising from the interventions.

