## Assignment of interventions: blinding

### Who will be blinded {17a}

The outcome assessors and data analyst will be blinded to the treatment assignment. The assessors will evaluate the clinical changes such as the POSAS scores and degree of erythema and pigmentation, as well as the area, thickness, and pliability of the keloid. As the intervention’s nature makes it impossible to blind participants and staff to the allocation, they are instructed not to disclose the participant’s allocation status during follow-up assessments. A computer IT assistant and other outcome assessors who assess the POSAS score and the degree of erythema and pigmentation, area, thickness, and pliability of keloid will anonymously be blinded to the intervention. They will record the results in anonymously case report forms (CRFs) and input data into separate datasheets online. This will enable the researcher to analyse data without accessing information about the allocation.

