## Data collection and management

### Plans for assessment and collection of outcomes {18a}

For the primary outcome, the evaluation analyses change in POSAS 3.0 scores over four periods, from the initial baseline to the final assessment conducted by a trained and blinded dermatologist to the interventions. After each review, a nurse assistant will collect the completed POSAS 3.0 forms attached in a CRF, and another non-research team member will input data online into an online form directly to the data analyst. The patient and observer scar assessment scale (POSAS) is a practical, comprehensive, and reliable measurement tool involving the perspectives of patients and doctors [57–59].

There are several measurements for secondary outcomes. A proficiently trained assistant, blinded to the intervention, will utilise dermoscopy to capture the colouration of the keloid. Subsequently, these images will be anonymously forwarded to a computer IT assistant for assessment of the degree of erythema and pigmentation using the ImageJ image analysis programme. After each process, the results will be recorded in a CRF and sent via an online form without any identifiable intervention to the data analyst. Measuring colours using ImageJ is comparable to measuring colour with a colourimeter [60, 61]. Taking pictures using a dermoscopy is not affected by distance and lighting because the dermoscopy has a fixed shooting distance and polarised lighting that comes directly from the device itself, so the pictures taken are more accurate than those that use a camera. Dermoscopy is a valid and reliable method for assessing the colour of both pigmentation due to the presence of melanin pigment and erythema caused by increased vascularity of scar tissue [62].

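### The protocol describes the POSAS primary outcome as assessed blind, but 16 of its 23 items (70% of the score range) are self-rated by participants who know their treatment

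*Protocol article*

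**What the plan says.** All sections are in the protocol article.

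- **What the primary outcome is.** Outcomes {12}: "The primary outcome directed towards the evaluation of POSAS 3.0 scores", measured at baseline and at weeks 4, 8 and 12.
- **Who rates it.** The same section says "Patients will complete the POSAS 3.0 questionnaire, which includes 16 items", of which five concern the present state of the scar and 11 the patient's feelings about it over the past week. Separately, "an observer will complete a different section of the questionnaire with seven items scored on a scale of 1 to 5".
- **How it is scored.** "The minimum patient score is 16, while the highest score is 80". "The minimum and maximum scores for observers are 7 and 35, respectively". The two parts are then combined: "We will add the PSAS and OSAS scores to determine the total score".
- **Who is blinded.** Who will be blinded {17a} twice lists POSAS among the measures evaluated by blinded outcome assessors. It also says that the intervention's "nature makes it impossible to blind participants and staff to the allocation".
- **How the primary assessment is described.** Plans for assessment and collection of outcomes {18a} describes the change in POSAS 3.0 as running "from the initial baseline to the final assessment conducted by a trained and blinded dermatologist to the interventions".
- **Separate use of the two parts.** The only one stated is a Pearson correlation for patient-observer agreement, under Methods for additional analyses {20b}.

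**The concern.** Sections {17a} and {18a} attach blinding to POSAS as a whole. Sections {12} and {17a} together show that most of the POSAS total comes from raters who know their treatment. Neither {17a} nor {18a} limits its statement to the observer part, so the article credits the primary outcome with a protection that most of the score does not have.

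This matters because the arms differ visibly: a gel that the patient applies twice daily, and an intralesional injection every 2 weeks. The article itself names injection pain and discomfort with needles as drawbacks of the comparator. Most patient items ask about feelings, which knowledge of treatment can colour. A between-group difference in the sum could then mix a change in the scar with a change in how patients report it. The stated agreement correlation estimates no treatment effect in either part, so it cannot separate the two.

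**Working it through.** **1. The plan's own figure.** Sample size {14} gives z-values of 1.96 and 0.84, SD 4.8, target difference 4 and correction factor Y = 0.8.

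- n = Y × 2 × [(1.96 + 0.84) × 4.8 / 4]² = 0.8 × 2 × 3.36² = 0.8 × 22.58 = 18.06. The stated 18 is this value rounded down; rounding up gives 19.
- With 20% dropout: 18 / (1 − 0.20) = 22.5, so 23 per group, as stated.

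The target of 4 points is therefore the yardstick for the primary score. I take it to refer to the summed score, since {12} defines no other total.

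**2. Share of the total that is self-rated** (ranges from {12}).

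- PSAS width: 80 − 16 = 64.
- OSAS width: 35 − 7 = 28.
- Total width: 64 + 28 = 92, running from 23 to 115.
- PSAS share: 64 / 92 = 69.6%. By number of items it is 16 / 23 = 69.6%, and by maximum score 80 / 115 = 69.6%.
- OSAS share: 28 / 92 = 30.4%.

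**3. Sensitivity of the total to differential reporting.** The documents give no size for such a bias, so the shifts below are assumptions. Each is an average between-group shift of b points on every PSAS item, with no true effect. The total moves by 16 × b. Treating Y as a variance factor, as the protocol's formula does, SE = 4.8 × √0.8 × √(2/n), which is 1.43 for n = 18 and 1.27 for n = 23. The two-sided rejection rate is Φ(16b/SE − 1.96) + Φ(−16b/SE − 1.96).

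| Assumed shift per item | Shift in total | Rejection rate, 18 per group | Rejection rate, 23 per group |
|---|---|---|---|
| 0 | 0 | 5% | 5% |
| 0.05 | 0.8 | 9% | 10% |
| 0.10 | 1.6 | 20% | 24% |
| 0.125 | 2.0 | 29% | 35% |
| 0.25 | 4.0 | 80% | 88% |

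The shift that reproduces the whole target difference is 4 / 16 = 0.25 point per item on a scale whose items run from 1 to 5. It is the top of the assumed range, not an estimate. The rates are the same for a shift in either direction.

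**4. What cannot be computed.** The article gives no SD or target difference for OSAS alone, so the power of an OSAS comparison with 23 per group is unknown.

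**The case against.** The strongest reply is that nothing is concealed. Trial design {8} calls the trial single-blind, {17a} says participants know their treatment, {12} says who completes which items, and {18a} itself notes that POSAS brings in the patient's view. This stands. A reader might infer that the unblinded self-rating is hidden or could not be detected, and the documents do not support that. The fault is one of description: the blinding statements do not exclude the patient part.

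Second, other blinded evidence exists. Erythema, pigmentation, area, thickness and pliability are to be assessed blind at the same four visits. This also stands, so OSAS is the only blinded part of the primary outcome, not of the trial. A result driven purely by self-report would lack support from these measures. They do not, however, make the statement about POSAS correct.

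Third, component analyses are often left to an analysis plan, and both parts are collected, so an OSAS comparison can be recovered. A reader might infer that summing the parts loses the blinded one or that OSAS will never be compared. The article does not exclude it, and its silence is not itself the fault.

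Fourth, a patient-reported primary outcome is a legitimate choice when a gel is compared with an injection, and {12} justifies it by its link to quality of life. Agreed: the point asks for accurate labelling, not for a different outcome.

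Fifth, the size of any bias is assumed. A reader might infer that dislike of needles will produce the whole target difference in favour of the gel. No document gives a size or a direction, and the injection is presented as the standard treatment, so expectations could also favour it.

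**Conclusion.** The point holds as an error in how the blinding of the primary outcome is described. The claim in {17a} and {18a} is right for OSAS, 7 items and 30% of the range, and wrong for PSAS, 16 items and 70%. These figures follow directly from {12} and rest on no assumption.

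The consequence is a possibility, not a demonstrated bias. The movement of 0.8 to 4.0 points rests on assumed uniform shifts of 0.05 to 0.25 per patient item, fully differential between arms and of unknown direction. Nor does 70% of the range mean 70% of the observed difference or of the variance, which the documents do not allow one to work out. What can be said is that small shifts would be material against a target of 4, and that a superiority result on the sum should not be presented as a blinded finding.

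**What to change.** - **Correct the text.** In {17a} and {18a}, restrict the blinding statements to OSAS and state that PSAS is self-reported by unblinded participants.
- **Pre-specify the components.** Keep the total as the primary score if wanted. Apply the same repeated-measures treatment comparison to OSAS and PSAS separately, with OSAS named as a key supporting analysis. Report estimates and confidence intervals for both.
- **State how they will be read.** Any superiority claim on the total should be interpreted alongside OSAS and the blinded secondary outcomes. I would not make the claim conditional on OSAS merely pointing the same way: with no true effect it would do so about half the time, so such a rule protects little. If OSAS were instead made primary, the sample size would need its own SD and target difference.
- **Optional safeguard.** Keep the completed PSAS sheet from the observer. Nothing in the article says that the observer sees it; {18a} has a nurse assistant collect the forms after each review.

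The cost is a few sentences and two extra models, with no new data. The drawback for the sponsor is a less favourable, but accurate, account of the blinding.
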